### Data Collection and Management

For all focus groups, each potential participant will first do a Zoom screening session where the consent form will be read to them; basic sociodemographic information (ie, age, gender, and race or ethnicity) will be collected; and they will be asked about their availability for the focus group from a list of potential dates and times. The consent form outlines the study’s components, the risks and benefits of enrollment, the length of time for the focus group process, the duration of the study, and contacts for the study and university should the participant have a question. As part of the consent form, participants will be informed that their “physical” identity will not remain anonymous with the other participants as they will see each other on Zoom or in person. Verbal informed consent will be obtained and recorded from eligible participants before starting the focus group.

Focus groups will be conducted either on Zoom or in person. For Zoom focus groups, each person will be sent an invitation to a password-protected Zoom room, and each will be added to the Zoom room one by one by the researchers, ensuring no names are shown on their profile. In-person focus groups will be hosted at UC San Diego, either in La Jolla or Hillcrest, depending on the participants’ preference, in a private room where others cannot listen in.

For all focus groups, a topic guide has been created that covers topics of the websites’ safety, acceptability, user experience, reach, usefulness, safety, and additional resources or suggestions that participants have (Multimedia Appendix 3). Focus groups will last for 60 to 90 minutes and will be audio recorded on a digital Dictaphone (no images or video will be recorded). Participants will be compensated with a US $20 debit card. Data from the focus groups will be kept on a password-protected computer with restricted access by the research team and transcribed.

Google Analytics will provide information on users’ general demographics, site of origin (Reddit or Google), and the time spent on each web page. All data analyzed to investigate the *MOUD Hub* dissemination potential are from Google Analytics and website traffic. Google Analytics will provide details about the users, such as whether they are new or returning; their session on the website; what website pages they visit; page views; and bounce rates, which is when a user visits a website and leaves without interacting with any other pages [42]. Data will be stored on a password-protected computer with restricted access to the research team. Access to the Google Analytics data is username- and password-protected.

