### Recruitment, Sample, and Participants

To evaluate the safety and preliminary acceptability before advertising the website, we will first carry out pilot focus groups with 10 graduate students with lived experience of OUD, personally or through family and friends, and who are participating in recovery groups or unions for people who use drugs. In these focus groups, we will pay particular attention to safety and make changes to the MOUD Hub accordingly. Participants will be recruited by contacting UC San Diego and San Diego State University student recovery groups.

After the pilot focus groups have been conducted and relevant changes have been made, 4 additional focus groups will be conducted with people living with OUD who have never received MOUD; people living with OUD who have experience with MOUD; family and friends of someone using opioids (including people living with OUD); and individuals who work with people living with OUD, including MOUD providers, counselors, and harm reduction workers. Each focus group will aim to have 4 to 8 participants. Participants will be recruited from MOUD treatment centers, support groups for family or friends of people living with OUD, and harm reduction organizations in San Diego through email to ask for permission to share study fliers. The purpose of these focus groups will be to gain more in-depth knowledge on the safety and acceptability of the hub, user experience, and thoughts on its usefulness in improving MOUD access and retention.

For all focus groups, participants will have the option of engaging in a focus group either through Zoom (Zoom Video Communications) or in person. Inclusion criteria for participants include being aged ≥18 years and having at least one of the aforementioned experiences. Exclusion criteria include experiencing severe mental health issues and being unable to provide informed consent.

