### Limitations

One key limitation of this study is recognizing that not everyone has access to the internet, and thereby, some people will be excluded from using the *MOUD Hub*. Those most vulnerable often lack regular access to the internet. Therefore, if the *MOUD Hub* was successful in supporting access to and retention in MOUD treatment, it could exacerbate existing disparities in MOUD coverage by socioeconomic and housing status. However, among those who are unhoused or not working, the internet can be more accessible compared to physical services, with recent studies finding that >50% of adults experiencing homelessness have phones with internet access [50].

Web-based platforms offer a lifeline or support to people who may not be able to access health care regularly. The internet is a powerful tool in helping patients collaborate with their physicians by being more active in decision-making, preparing for their appointments, and facilitating communication [22].

Another limitation at this stage is that the website is not interactive, thus losing parts of the spirit of MI that can only be done through a person-to-person conversation. However, we are using elements of MI that might help the website users take the first step to receive the support needed. For example, we provide education and MI check-in questions tailored for each stage, including decisional balance questions and readiness and confidence rulers. Users will be encouraged to write their reflections on these questions in the space provided, and the website allows them to download their responses for them to keep. It is well established that information is not enough to elicit behavior change and that other issues take over when it comes to accessing SUD treatment (and other health interventions). However, we are providing concrete resources to address mistrust and logistical issues and ensuring that people with OUD, as well as their friends and family, are well equipped to understand how MOUD works and how to access and remain on treatment as an important first step.

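### Zoom-only screening makes the ability to complete a Zoom session an unlisted entry condition for every focus group, including those held in person

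*Protocol article*

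**What the plan says.** Data Collection and Management sets one screening route and applies it to every focus group: "each potential participant will first do a Zoom screening session where the consent form will be read to them". In that session staff also take age, gender and race or ethnicity, and ask which of the offered dates suit the candidate. Verbal consent is then obtained and recorded before the focus group starts.

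Recruitment, Sample, and Participants sets how people attend: "participants will have the option of engaging in a focus group either through Zoom (Zoom Video Communications) or in person". The eligibility criteria follow directly. On who may enter, the section reads: "Inclusion criteria for participants include being aged ≥18 years and having at least one of the aforementioned experiences". On who may not, the next sentence reads: "Exclusion criteria include experiencing severe mental health issues and being unable to provide informed consent". Neither sentence refers to Zoom, a device or an internet connection. For the four groups that follow the pilot, the recruitment sources are described thus: "Participants will be recruited from MOUD treatment centers, support groups for family or friends of people living with OUD, and harm reduction organizations".

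Limitations acknowledges uneven access: "Those most vulnerable often lack regular access to the internet". It raises this as a limit on who can use the website. It adds that more than 50% of "adults experiencing homelessness have phones with internet access".

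**The concern.** The screening rule applies to every candidate and comes before any group. A person can satisfy each listed criterion, be willing to travel to an in-person session, and still not enter the study because the one route into it runs through Zoom. The criteria as printed therefore do not fully describe who can be enrolled.

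What is at stake is who speaks in the focus groups. They are the only data collection from prospective users that the plan describes before launch, and Ethical Considerations relies on them for the assessment of safety. Google Analytics and the exit survey come later and observe only people who have already reached the site. If poorly connected people with OUD are less likely to get through screening, their views on safety, usability and acceptability are under-represented when the site is revised before launch. The later data are not designed to make up for that. The article discusses selection among website visitors and survey respondents, but not selection into the focus groups.

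**Working it through.** No formula applies and the plan gives no figure to reproduce. The check sets the statements side by side.

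1. **Scope of the screening rule.** Data Collection and Management applies it to all focus groups and to each potential participant, as the first step. No exception is made for those who will attend in person, and no other mode is named. This is a stated rule, not a silence.

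2. **Listed criteria.** The inclusion criteria are age 18 or over and at least one of the named experiences. The exclusions are severe mental health issues and inability to consent. Zoom or internet access is in neither list.

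3. **Combining 1 and 2.** Someone who meets every listed criterion and could attend in person, but cannot complete a Zoom session, cannot be screened and so cannot enrol. The ability to complete the session acts as an additional, unlisted criterion.

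4. **Compatibility with the in-person option.** The attendance choice concerns the focus group; the Zoom rule concerns the earlier screening step. A candidate can be screened on Zoom and then attend in person, so both statements can be carried out as written. There is no contradiction.

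5. **Who is most likely to be affected.** The two pilot groups consist of graduate students, and one of the four later groups consists of people who work with patients. Another consists of family and friends, which may include some people living with OUD. The effect, if any, falls mainly on the two groups of people living with OUD (with and without experience of medication treatment), recruited in part through treatment centers and harm reduction organizations. At 4 to 8 participants each, these two groups hold 2 × 4 = 8 to 2 × 8 = 16 people.

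6. **Size of the effect.** It would require the share of otherwise eligible candidates who cannot complete a Zoom session. The article does not give it. Its only access figure, more than 50%, concerns phones with internet access among adults experiencing homelessness. That is a different population from focus-group candidates, and having such a phone is not the same as being able to complete a Zoom session. It also takes no account of access by other means. The number lost to screening cannot be derived.

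7. **Whether the tasks need Zoom.** Screening consists of reading a form aloud, taking three demographic items and asking about availability. None of these requires video. Because availability is collected here, however, screening has to take place before the groups are scheduled.

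**The case against.** The strongest reply has four parts.

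- **The two rules are consistent.** A reader might infer that Zoom screening contradicts or cancels the in-person option. The text does not support that. The steps are separate, and nothing says that the in-person groups were set up for people without Zoom. The only preference mentioned in the in-person arrangements concerns which of two sites to use. The option remains open to anyone who completes one call and prefers to meet face to face. This part stands in full.

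- **The barrier may be low.** The article asks for a Zoom session. It does not ask for a private video call, a data plan or a candidate's own device. It does not say whether a recruiting organization could help someone join, and it does not rule this out. This stands, and it is one reason why no number can be attached. A reader might also infer from the phone figure that up to nearly half of candidates would be lost; that figure does not describe candidates and cannot carry such an estimate.

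- **The groups evaluate a website, so its users need some internet access anyway.** This limits the consequence but does not remove it. Opening a page on a shared or public connection asks less of a person than keeping a scheduled session that covers consent and demographics. The article itself shows interest in people who use the internet in public spaces when it discusses a future trial.

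- **Contact modes for screening are logistics that an article leaves to the full protocol.** This would answer a complaint that the article is silent. It does not answer the present point, because the article fixes the mode for every candidate and separately prints criteria that omit it.

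**Conclusion.** The point holds in a limited form. As written, completing a Zoom session is a condition of entry to every focus group, including those held in person, and the eligibility criteria do not list it. It may select against poorly connected people with OUD, chiefly in the two groups of people living with OUD.

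The conclusion that the condition exists rests only on the wording of the screening rule and the criteria. The conclusion that it may matter rests on two assumptions: that some otherwise eligible people at the recruiting sites cannot complete a Zoom session, and that they are not routinely helped to do so. The article neither confirms nor excludes either one. Its own remark on internet access among the most vulnerable makes the first plausible.

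Severity is minor. The focus groups are small and qualitative, the study has no target sample size, and no outcome definition, analysis or statistical figure is affected. The point is worth acting on because the selection is avoidable at almost no cost, and because the article acknowledges the access gap only for use of the website.

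**What to change.** In Data Collection and Management, change the screening sentence so that screening and reading of the consent form can be done by Zoom or by telephone, or in person where convenient. Keep it ahead of scheduling, since the session also collects availability; screening on arrival at the group would not fit that purpose. Record the screening mode for each participant so that its use can be reported by group.

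If Zoom-only screening is kept, add it as a requirement to the criteria in Recruitment, Sample, and Participants, and state in Limitations that it may select focus-group members by connectivity.

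The cost is a small change of wording in the protocol and recruitment material, one recorded item per participant, and slightly less convenient scheduling for staff.

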**Objective:**

This study aims to assess the safety, acceptability, feasibility of dissemination, and reach of the *MOUD Hub* using focus groups and advertising on 1 key search engine and 1 social media platform.

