**Methods:**

This protocol describes the development of the *MOUD Hub* and the descriptive observational feasibility study that will be undertaken. The *MOUD Hub* uses motivational interviewing principles to guide users through the stages of change. The website provides evidence-based information from national health and substance use agencies, harm reduction organizations, and peer-reviewed literature. First, pilot focus groups with 10 graduate students who have lived experience with OUD will be conducted to provide feedback on safety concerns. Then, focus groups with 20-30 potential *MOUD Hub* users (eg, people with OUD with and without MOUD experience, friends and family, and health care providers) will be conducted to assess safety, acceptability, reach, and usability. Data will be analyzed using inductive thematic analysis. The website will be advertised on Google and MOUD-specific Reddit forums to assess dissemination, reach, and user acceptability based on the total user volume, sociodemographic characteristics, pop-up survey responses, and 1-year engagement patterns. This information will be collected through Google Analytics. Potential differences between users from Google and Reddit will be assessed.

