There are no eligibility criteria for the study when assessing the website’s reach due to it being available for public access. We will be openly advertising it to people who make relevant Google searches or who are members of opioid-related subreddits. Similarly, there is no randomization, as all users can access the same website’s content. We will be able to identify whether participants came from Reddit or Google and treat them as 2 different samples. This will enable us to investigate differences in user volume and characteristics when accessing the website through Reddit or Google and to evaluate the most appropriate platform for dissemination for future-related interventions.

There is potential for bias, including misclassification, self-selection, and response bias. It will not be possible to know whether users are experiencing OUD or searching for information for a loved one, limiting our understanding of the representativity of the sample by OUD experience and leading to potential misclassification bias. However, we will be able to know whether users clicked on resources specific to friends or family and whether they responded to the “check-in” questions directed at people living with OUD. In addition, the pop-up survey asks whether users are accessing the website for themselves or a friend or family member. This will provide us with an additional measure for the proportion of users who are seeking help for themselves versus for a friend or family member.

Effectively, all people accessing the website will self-select based on need or curiosity, and we will miss information from people living with OUD who are not seeking help for OUD or are not compelled to access the *MOUD Hub* when exposed to it. The demographics data will allow us to assess to what extent our sample is representative of the general population and the population experiencing OUD and fatal overdoses in the United States in terms of geography, age, and gender. We will also be able to assess whether users are accessing the website from Google, Reddit, or other sources, potentially representing different communities. While response bias is possible in the context of our pop-up survey, participation will be voluntary and anonymous, and therefore, this will be minimized. However, there will undoubtedly be self-selection bias among the group answering the survey, likely representing those most engaged in improving access to reliable MOUD information*.*

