**Quantitative measures**		
	Volume of users (GA^a^)	Proportion of users who return to the website (GA)
	Average time spent on the website (GA)	Acceptability of Intervention Measure questions (PS^b^; Figure 4)
	The average number of resources the users clicked on in different stages (GA)	—^c^
	Total number of times a resource was clicked within each stage (GA)	—
	User demographics (age, gender, location, language, and accessing the website for themselves or for a friend or family member; GA and PS)	—

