### Statistical and Qualitative Analyses

Focus group transcripts will be analyzed using inductive thematic analysis. This inductive approach is useful when using direct questions to describe a particular experience and find common themes within data [43]. Two researchers will go through multiple coding iterations, with the first consisting of coding the data without preconceived categories. After the first round of coding, the researchers will decide on what codes to use and apply finalized codes using Atlas.ti (Lumivero) software [44]. Consistency will be achieved through regular team meetings, coding disagreements will be resolved through team deliberation, and code definitions will be enhanced as needed [45,46]. An in-depth review of coded data will lead to the identification of themes related to the safety, acceptability, and potential reach of the MOUD Hub and its hypothesized usefulness in improving access to and retention in MOUD treatment. We will then conduct member checking with selected participants to reduce the risk of data misinterpretation [47,48]. We will keep a log of suggestions and reasons regarding why they were or were not implemented.

Open-ended responses to the pop-up survey in the MOUD Hub will be analyzed on Atlas.ti software by the same 2 researchers using deductive-inductive thematic analysis based on the codebook developed for the analysis of the focus groups’ data but allowing for new codes to emerge [49]. The same process will be followed to reach a consensus on the coding and to identify themes to answer our research questions.

Descriptive statistics will be conducted to assess the population that has accessed the website, their website of origin (Reddit or Google), how long participants were on the website, and how many pages they visited. Descriptive statistics will include the percentages, means, and SDs of age, gender, and geographic location of users. Descriptive statistics on how long participants were on the website and how many pages they visited will be measured by the total number of times the web page was visited, how many pages were visited, and the proportion of returning users. Descriptive statistics on the mean and SD of responses to the Acceptability of Intervention Measure will be assessed, with a mean between 4 and 5, corresponding to the “agree” and “completely agree” options in the scale, interpreted as users finding the website acceptable. We will produce CIs for each outcome.

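### Recording only the site of origin mixes arrivals from the Google adverts and subreddit posts with other Google and Reddit traffic, so the platform comparison cannot show what the advertising achieved

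*Protocol article*

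**What the plan says.** The Objective in the abstract is to assess safety, acceptability, feasibility of dissemination and reach "using focus groups and advertising on 1 key search engine and 1 social media platform". The abstract's Methods say that the site will be advertised on Google and on Reddit forums "to assess dissemination, reach, and user acceptability based on the total user volume", together with user characteristics, survey responses and engagement. The Dissemination section describes the two routes: adverts shown in response to chosen Google searches, and a monthly post in each of four named subreddits.

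The source of a visit is recorded at site level. Data Collection and Management gives "site of origin (Reddit or Google"), and Statistical and Qualitative Analyses gives "their website of origin (Reddit or Google"). Recruitment, Sample, and Participants treats Reddit and Google users as two samples. Two paragraphs later it says the team can see "whether users are accessing the website from Google, Reddit, or other sources".

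That section also says that the Reddit-Google comparison will help to identify the most suitable platform for disseminating future interventions. Outcomes and Measures uses it to compare how effectively social media and search engines spread such a resource.

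**The concern.** The team will run two dissemination activities and then recommend a platform. To support that recommendation the data should show how many users each activity brought in. Site of origin shows only which platform a user arrived from.

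The article itself makes other arrivals foreseeable. The site is open to the public, it is referenced in the published protocol, and focus-group participants will have seen it before launch. Anyone who hears of it this way and later searches its name is counted under Google. The Introduction lists r/OpioidRecovery among the relevant forums, but the Dissemination section does not plan posts there. A link that a user shares in that forum is counted under Reddit.

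If such arrivals are unevenly spread between the two sites, a difference in volume could reflect background traffic and not the adverts or posts. A later team that plans its advertising on this result could choose the wrong channel. Visits that carry no marker on arrival may not be separable afterwards, so the matter has to be settled before launch.

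**Working it through.** The plan states no user volume, expected ratio or share of unadvertised traffic, so there is no figure of its own to reproduce. The check has two parts.

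**1. The sections side by side**

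- *What is done:* Google adverts on chosen search terms, and monthly posts in four subreddits (Dissemination).
- *What is counted:* all users (Table 2), and users by Reddit or Google (Data Collection and Management; Statistical and Qualitative Analyses).
- *Where the counts come from:* Data Collection and Management says that all data on dissemination potential come from Google Analytics and website traffic. The article names no click count from the advert platform that could fill the gap.
- *What is concluded:* the most suitable dissemination platform (Recruitment, Sample, and Participants; Outcomes and Measures).

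No section separates an arrival through an advert or study post from another arrival from the same site. The step from what is counted to what is concluded therefore rests on an unstated assumption: that unadvertised arrivals are few, or form a similar share of each platform's traffic.

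**2. How much mixing would matter (all shares assumed)**

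Let R be the observed ratio of Google to Reddit users by site of origin. Let g and r be the unadvertised shares of Google and Reddit arrivals. Then

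ratio among advert- and post-generated users = R × (1 − g) / (1 − r).

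This falls below 1 when g > 1 − (1 − r) / R.

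| R | Reverses if g exceeds (r = 0) | Reverses if g exceeds (r = 0.1) |
|---|---|---|
| 1.2 | 1 − 1/1.2 = 16.7% | 1 − 0.9/1.2 = 25% |
| 1.5 | 33.3% | 40% |
| 2 | 50% | 55% |
| 3 | 66.7% | 70% |

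The mixing can also work the other way. With R = 1.2, g = 0 and r = 0.1, the ratio among generated users is 1.2/0.9 = 1.33, so site of origin would understate the lead of the Google adverts. The direction is not known in advance.

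For the gap between total traffic and advert- or post-generated traffic, take 1,000 users, a share h from other sources, and the same unadvertised share u on both platforms. Generated users = 1,000 × (1 − h) × (1 − u).

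- h = 0, u = 0: 1,000 users, so total/generated = 1.00.
- h = 10%, u = 20%: 1,000 × 0.9 × 0.8 = 720, so total/generated = 1.39.
- h = 30%, u = 50%: 1,000 × 0.7 × 0.5 = 350, so total/generated = 2.86.

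These figures show sensitivity only. A clear lead for one platform would survive moderate mixing. A narrow lead would not.

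**The case against.** The strongest reply is that the study asks about the website and its platforms, and not about its adverts. The stated aims are user volume, user characteristics, patterns of use, and differences between those arriving from Google and from Reddit. Reach is defined as the number, proportion and representativeness of people willing to take part. Total volume measures that directly, and this part of the reply stands.

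A reader might infer that unadvertised traffic could make reach hypothesis 3 come out falsely supported. The documents do not bear this out. The hypothesis concerns users referred through Google searches and through Reddit. Someone who clicks an unadvertised result was still referred by a Google search, and a reshared link is still Reddit traffic. A reversal among advert- and post-generated users would answer a different question.

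A reader might also infer that the article credits every arrival to its adverts, or that it wrongly drops a third group. It never says the first. On the second, it acknowledges users "accessing the website from Google, Reddit, or other sources", and a contrast of two named platforms need not include a third. What remains is a mismatch of wording between sections.

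Finally, link tagging may be set out in a fuller document that is not shown, and its absence from an article would be no fault in itself. However, this article does define the source variable, in two places and at site level, and then rests a dissemination recommendation on it.

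**Conclusion.** The point holds as an inexpensive improvement, and not as an error in a stated hypothesis. As described, the Reddit-Google comparison is a valid platform-level description, but it cannot show what the adverts and posts achieved. The article uses it to recommend a dissemination platform after disseminating by those means.

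The size of the mixing is unknown. On the assumed shares, total traffic is 1.00 to 2.86 times the advert- and post-generated traffic. With no unadvertised Reddit arrivals, a Google lead of 1.2 to 1.5 would reverse among generated users at unadvertised Google shares above 16.7% to 33.3%. Nothing in the article shows that shares of this order will occur, and the lower end of the range is no distortion at all.

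The conclusion rests on reading the recommendation as guidance on where to advertise or post. If the team means only which platform visitors come from, by any route, the comparison by site of origin is sufficient and the article should say so.

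**What to change.** - Before launch, give the Google advert its own tagged link, and give each monthly subreddit post another. One post per subreddit per month for a year makes 4 × 12 = 48 post links.
- Keep total user volume as the measure of overall website reach, and keep the platform-level comparison for hypothesis 3.
- Add a Reddit-Google comparison restricted to tagged arrivals, and name it as the basis for the dissemination-platform recommendation.
- Report untagged Google, untagged Reddit and other arrivals as separate rows, within total volume but outside the tagged comparison.
- Align the source categories in Data Collection and Management and in Statistical and Qualitative Analyses with the three named in Recruitment, Sample, and Participants.

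The cost is minor set-up work and a few changed sentences. Reported advert reach will be lower than total traffic. It will also miss people who saw an advert or post but arrived by another route, so it should be presented as a count of direct arrivals and not as the full effect of the advertising.
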